### Participants and recruitment

The PRePP-project aims to include two samples of participants, patients and their respective care providers. It aims to include consecutively 240 patients and, if present and consenting, their respective primary IC within 18 months.

Eligible patients who are adult (> 17 years), suffer from an advanced, life-limiting disease and are treated by the SAPV-team of our institution will be included.

The primary non-professional caregiver is defined as the adult person that provides most time supporting the patient regardless of being biological related or non-related. ICs can participate if they provide informed consent, are mentally and linguistically able to provide answers independently. IC-reported data can only be collected for patients with consenting ICs. Due to this condition the exact number of IC-participants cannot be predicted.

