Medical records will provide routinely assessed information concerning characteristics of patient such as age, gender, diagnosis, duration of previous hospitalization, additional supportive services, number of visits by SAPV, symptoms status, admission (e.g. reasons, initiating person, admitting physician, planned vs. unplanned, which procedures applied).

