### Statistical analysis

The primary endpoint "number of unplanned inpatient admissions" is account variable. Univariate Poisson regressions will be used to analyze the association of structural factors and relative-reported factors or structural data with the primary endpoint. With the planned patient number of 240, it is possible to detect changes of 50% (corresponding to rate ratios of 1.5 and greater, given a base rate of 0.85) with a power of 95% if the influence variable is a binary categorical variable with 50% probability of occurrence. For a binary factor with a probability of occurrence of 90%, the detectable rate ratio with 95% power is still 2.0. For continuous, normally distributed influence variables, rate ratios of > 1.25 are detectable with 95% power.

Since a large number of factors are to be tested, the adjustment for multiple testing seems reasonable. According to the explorative approach of the study, the control of the false discovery rate is done by Benjamini–Hochberg procedure. *P* values of the univariate regression analyses that are < 0.05 after adjustment with the Benjamini–Hochberg procedure are considered significant. In the multivariable model, all parameters whose *p* values from the univariate analyses are < 0.1 after adjustment should be analyzed. The *p*-values of the multivariable model will not be adjusted.

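### The primary endpoint is a count of unplanned admissions with no time at risk; run as written, the Poisson model mixes survival with admission rate

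*Protocol article*

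**What the plan says.** All of the following is in the protocol article, under Methods/design.

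- **Endpoint and model (Statistical analysis).** The primary endpoint is the "number of unplanned inpatient admissions", treated as a count. The model is given as: "Univariate Poisson regressions will be used to analyze the association of structural factors and relative-reported factors or structural data with the primary endpoint".
- **Power (Statistical analysis).** "With the planned patient number of 240, it is possible to detect changes of 50" percent, "corresponding to rate ratios of 1.5 and greater, given a base rate of 0.85) with a power of 95" percent, for a binary factor present in half the patients. Two further statements use the same scale: "For a binary factor with a probability of occurrence of 90%, the detectable rate ratio with 95% power is still 2.0" and "For continuous, normally distributed influence variables, rate ratios of > 1.25 are detectable with 95% power". The 0.85 carries no unit of time.
- **Population (Participants and recruitment).** Eligible adults "suffer from an advanced, life-limiting disease and are treated by the SAPV-team of our institution".
- **Follow-up (Study visits and data assessment).** Medical-record and nurse-reported data are collected monthly from T1 to T7, with T7 at six months.
- **Death.** The abstract lists nurse reports on whether death was unexpected. Study measures has nurses judge whether death within the coming month would surprise them.
- **Candidate predictors (Study measures).** These include age, diagnosis and "number of visits by SAPV, symptoms status".

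The article does not say over what period admissions are counted, how long each patient is at risk, or what happens to the count when a patient dies.

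**The concern.** A patient who dies two weeks after T1 has had far less opportunity to be admitted than one followed to T7. If both contribute a bare count, the model estimates a ratio of mean counts, which is the admission rate multiplied by time under observation. A factor that goes with shorter survival then appears to go with fewer unplanned admissions, and a factor that truly raises the admission rate while shortening survival can be hidden. Diagnosis, age and symptom status are plausibly of this kind.

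This affects every univariate test of the primary endpoint. The Benjamini-Hochberg adjustment controls the false discovery rate; it does not remove bias. The screen at an adjusted p below 0.1 would then carry affected factors into the multivariable model.

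The section is also not coherent as it stands. A rate ratio needs a time base. If an offset is intended, 0.85 needs a unit and the power needs expected person-time. If none is intended, the effect measure is a ratio of mean counts and should be called that.

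**Working it through.** **1. The plan's own power figure.** Inputs from Statistical analysis: N = 240, base rate b = 0.85, RR = 1.5, factor prevalence π = 0.5. The level is 0.05; sidedness is not stated. Every patient is given exposure 1.

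Power = Φ( √(N·b)·ln RR / √V − z ), with V = 1/(1−π) + 1/(π·RR).

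- V = 2 + 1.333 = 3.333; √(240 × 0.85) = √204 = 14.283; ln 1.5 = 0.4055.
- 14.283 × 0.4055 / 1.826 = 3.172.
- One-sided: Φ(3.172 − 1.645) = 0.937. Two-sided: Φ(3.172 − 1.960) = 0.887.

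So the stated 95% is approximately reached only with equal exposure for everyone and a one-sided test. The sidedness is a separate matter. What counts here is that the figure makes no allowance for unequal follow-up.

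**2. Time at risk (assumption).** The documents give no survival figure, so I assume exponential survival with median m months, cut at six months: E[T] = (1 − e^(−6h))/h, with h = ln 2/m.

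| Median (months) | E[T] (months) | Share of six months |
|---|---|---|
| 2 | 2.525 | 42% |
| 3 | 3.246 | 54% |
| 4 | 3.731 | 62% |
| 6 | 4.328 | 72% |
| 12 | 5.071 | 85% |

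**3. Apparent ratio without an offset.** If the factor has no effect on a constant monthly admission rate, the ratio of mean counts is E[T | factor] / E[T | no factor]. The rejection column is simulated for N = 240, a 50% factor and an overall mean count of 0.85, at two-sided p < 0.05 before any multiplicity adjustment.

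| Medians without vs with factor | Apparent ratio | Nominal rejection |
|---|---|---|
| 4 vs 2 | 2.525/3.731 = 0.68 | 75% |
| 6 vs 3 | 3.246/4.328 = 0.75 | 52% |
| 12 vs 6 | 4.328/5.071 = 0.85 | 23% |
| 3 vs 2 | 2.525/3.246 = 0.78 | 44% |

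The first three rows halve the median. With shorter survival the distortion is larger: 3 vs 1.5 months gives 0.625.

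A true rate ratio of 1.5 with medians of 4 vs 2 shows as 1.5 × 0.677 = 1.02. With log(time at risk) as an offset, the estimates are 1.00 (about 5% rejection) in the null case and 1.50 in the other.

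**4. A factor unrelated to survival.** There is no bias. Unequal follow-up adds variance that the Poisson standard error ignores, so nominal rejection is about 8% with a median of 4 months in both groups and about 11% with a median of 2.

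**5. Power if 0.85 is a six-month rate (assumption).** Replace b by 0.85 × the share in step 2. Two-sided power for RR 1.5 falls from 0.887 to 0.54 (median 2), 0.71 (median 4) or 0.83 (median 12).

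**6. Limit of the offset.** Suppose the admission rate triples in the last month of life and the factor affects survival only. Medians of 4 vs 2 then give 0.81 without an offset and 1.20 with it; 6 vs 3 give 0.87 and 1.16. With a fivefold rise, 4 vs 2 gives 0.90 and 1.33.

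**The case against.** **Silence is not a decision.** A reader might infer that the sponsor has chosen to analyse without an offset. The documents do not support that: no sentence excludes one, the terms rate ratio and base rate are compatible with one, and a condensed article may leave a model term to a fuller plan. This objection stands, and the point is limited to what the article fixes. The time base of the primary endpoint and the unit of its base rate belong to the definition and to the power statement, and both are in the article without them.

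**The raw count may be intended.** The expected number of admissions up to death or six months is a usable predictive quantity, and the aim is prediction with a view to a screening tool. This is a fair possibility, but the article does not state it, and its effect measure would then be misnamed.

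**The sizes rest on assumptions.** This also stands. The scenarios assume that a factor shifts median survival 1.5- to 2-fold. Caregiver-related and structural factors may not do that, and a factor unrelated to survival is unbiased. The rejection figures are before the planned Benjamini-Hochberg adjustment; in the 4 vs 2 case, rejection drops to 56% at p < 0.01.

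**SAPV visits.** It is tempting to read the visit number as a total that grows with survival. The article does not say so, and with monthly collection it may be a monthly count.

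**An offset is not a complete remedy.** Step 6 shows that it can reverse the bias if admissions cluster before death. The fix allows for this.

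**Conclusion.** The point holds as a defect in how the primary endpoint, its effect measure and its power are defined. Run as written, the analysis mixes survival with admission rate. Under exponential survival and a constant admission rate, halving median survival from 4 to 12 months produces an apparent ratio of about 0.68 to 0.85 where none exists, and at the lower end this is as large as the effect the study is sized for (1/1.5 = 0.67). Factors unrelated to survival keep an unbiased estimate but are tested at about 8% rather than 5%, given a median of 4 months. The true size cannot be known from the documents. They do not support reading the article as a refusal of an offset, nor the claim that all predictors will be distorted.

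**What to change.** - Define the observation window for each patient, for example from T1 to death, end of SAPV care or T7, whichever comes first.
- Include log(time at risk) as an offset in the univariate and multivariable Poisson models.
- State the base rate of 0.85 per unit of person-time, and restate the power on expected person-time, with the survival assumption shown.
- Report raw counts and the number of deaths beside the rates, and show the raw-count regression as a sensitivity analysis.
- If the SAPV visit number is a total over follow-up, express it per unit of time.

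The cost is one model term, a few sentences and a recalculated power statement. The dates needed should be in the medical records. The downside is that the offset model estimates the rate while alive and does not by itself deal with death as a terminal event, notably if admission risk rises near death. The raw-count result is kept alongside for that reason.

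### The stated 95% power for rate ratios of 1.5 (50% binary factor) and 1.25 (continuous factor) is about 89–90% under an ordinary two-sided 5% test with 240 patients

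*Protocol article*

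**What the plan says.** The Statistical analysis section of the protocol article specifies univariate Poisson regressions of the number of unplanned admissions on each candidate factor. It gives three power figures for 240 patients:

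- Binary factor present in half the patients: the study can "detect changes of 50% (corresponding to rate ratios of 1.5 and greater, given a base rate of 0.85) with a power of 95" per cent.
- Binary factor present in nine patients out of ten: "For a binary factor with a probability of occurrence of 90%, the detectable rate ratio with 95% power is still 2.0".
- Continuous factor: "For continuous, normally distributed influence variables, rate ratios of > 1.25 are detectable with 95% power".

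No significance level or sidedness accompanies these figures, and 0.85 has no time unit. The only significance rule in the section concerns p-values from the "univariate regression analyses that are < 0.05 after adjustment with the Benjamini–Hochberg procedure are considered significant".

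**The concern.** A regression p-value compared with 0.05 is normally two-sided. On that reading, the inputs printed for the first and third bullets do not give 95% power.

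Nothing in the article points to one-sided testing. The approach is described as exploratory, and the candidate factors run in both directions. The Background links a palliative care consultation after discharge to fewer unplanned admissions, and suggests that an exhausted or ill caregiver may contribute to readmission. Under Study measures, a higher quality-of-life score is favourable while higher anxiety and depression scores are not.

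These figures are the only justification of the sample size in the article. If they are too high, the chance of missing a real effect of the stated size is about twice what a reader would assume.

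**Working it through.** **Inputs from the Statistical analysis section.** N = 240; base rate b = 0.85; rate ratio (RR) 1.5 at prevalence 50%; RR 2.0 at prevalence 90%; RR 1.25 for a normally distributed factor.

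**Assumptions, because the article is silent.** Exposure of 1 per patient; 0.85 is the rate in the reference group; variance equals the mean; RR 1.25 is per standard deviation (SD); level 5% per test before any multiplicity adjustment.

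**Formula for a binary factor (Wald).** Power = Φ(ln RR / SE − z), with SE = √(1/E₀ + 1/E₁), where E₀ and E₁ are the expected event counts in the two groups. z is 1.645 one-sided and 1.960 two-sided.

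**RR 1.5, 50% factor.**
- E₀ = 120 × 0.85 = 102; E₁ = 120 × 0.85 × 1.5 = 153.
- SE = √(1/102 + 1/153) = 0.1278; ln 1.5 / SE = 0.4055 / 0.1278 = 3.172.
- Closest to the plan's figure, one-sided 5%: Φ(3.172 − 1.645) = 93.7% (91.5–94.1% across formulas).
- Two-sided 5%: Φ(3.172 − 1.960) = 88.7%. Other formulas (null variance at the base rate, pooled variance, rate-difference score, square-root transform) give 84.7–89.5%. Simulated Wald, score and likelihood-ratio tests give 89–90%, and an exact conditional test 88.2%.
- RR with 95% power two-sided at N = 240: at RR 1.58, SE = 0.1265 and Φ(0.4574 / 0.1265 − 1.960) = 95%. Other formulas give 1.57–1.62.

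**RR 1.25 per SD, continuous factor.**
- β = ln 1.25 = 0.2231; information = N·b·exp(β²/2) = 204 × 1.0252 = 209.1; β × √209.1 = 3.227.
- One-sided 5%: Φ(3.227 − 1.645) = 94.3%.
- Two-sided 5%: Φ(3.227 − 1.960) = 89.7%; 89.3% with the null variance.
- RR with 95% power two-sided: about 1.28.

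**RR 2.0, 90% factor.**
- E₀ = 24 × 0.85 = 20.4; E₁ = 216 × 1.70 = 367.2; SE = 0.2275; ln 2 / SE = 3.047.
- Wald formula, two-sided: Φ(3.047 − 1.960) = 86.2%.
- Pooled-variance, score and square-root formulas, two-sided: 93.4–94.4%.
- Simulated two-sided tests with the split fixed at 216/24: likelihood-ratio 94.6%, score 93.2%, Wald 93.0%. If the split varies at random around 90%, these fall to about 93.4%, 91.8% and 91.5%.
- With only about 20 expected events in the smaller group, the Wald formula is a poor guide here.

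**Other readings of the inputs for RR 1.5, two-sided Wald.**
- 0.85 as the overall mean rate: 81.0%.
- 0.85 as the rate in the exposed group: 73.6%.
- Mean exposure needed to restore 95%: (1.960 + 1.645)² × 0.01634 / 0.4055² = 1.29 units. The article states no such exposure.

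**Multiplicity, for illustration only.** At assumed per-test two-sided levels of 0.01 and 0.0025, power for RR 1.5 is Φ(3.172 − 2.576) = 72% and Φ(3.172 − 3.023) = 56%.

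**The case against.** The strongest defence is that the article does not contradict itself. It never says the power figures are two-sided, and a one-sided 5% level comes within about one to two points of 95% for RR 1.5 and RR 1.25 by most formulas. The level may be recorded in a full protocol or analysis plan that is not shown. This stands in part: two-sided testing is inferred from the exploratory purpose and from factors that can act either way. That a one-sided level was used is equally an inference. It does not rescue the printed figures, since a reader of this article will take them to describe the regression p-values it plans.

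The unit of 0.85 is also open, and a mean exposure of about 1.29 would restore 95%. Exposure of 1 must therefore be declared as an assumption, but nothing in the text supplies the larger value. Nor does reading a 50% change as a halving help: it would have 98.1% power two-sided, but the text specifies rate ratios of 1.5 and greater.

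The objection succeeds on the third figure. A reader might infer that all three figures fail, or that all three come close only under a one-sided test. The working does not support that: for RR 2.0 with a 90% factor, two-sided likelihood-ratio and score tests come within about two points of 95% with the split fixed at 216/24. The low value of 86% belongs to the Wald formula.

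Finally, the study is exploratory and the detectable rate ratios move little (1.5 to 1.58, and 1.25 to 1.28). That limits the severity; it does not make the stated power correct.

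**Conclusion.** The point holds for two of the three figures. Under an unadjusted two-sided 5% test, power is about 89% for RR 1.5 with a 50% factor (85–89% across formulas) and about 90% for RR 1.25 per SD. The chance of missing such an effect is therefore about 11% (100 − 88.7 = 11.3) and 10% (100 − 89.7 = 10.3), against the stated 5%. The figure for RR 2.0 with a 90% factor is not shown to be wrong.

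This rests on plain Poisson variance, exposure of 1, 0.85 as the reference-group rate and RR 1.25 taken per SD. The two alternative readings of 0.85 make the shortfall larger. The planned Benjamini–Hochberg adjustment can only lower the power for each factor further.

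A reader might also infer that 240 patients are too few and that recruitment must rise; about 310 would be needed for 95% two-sided power at RR 1.5. The article does not support that step: nothing in an exploratory study requires 95%, and about 89% is still good power. The defect lies in the stated figure and its undeclared error level. Severity is moderate.

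**What to change.** In the Statistical analysis section:

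1. State that the power figures assume a two-sided level of 0.05 per test before Benjamini–Hochberg adjustment, exposure of 1 per patient and a reference-group rate of 0.85.
2. Restate power with 240 patients as about 89% for RR 1.5 with a 50% factor (95% power at RR about 1.58).
3. Restate it as about 90% for RR 1.25 per SD of a continuous factor (95% power at about 1.28 per SD).
4. Keep RR 2.0 for the 90% factor, giving its power as about 93–95% for a fixed 216/24 split and naming the test (likelihood-ratio or score).
5. Add that the Benjamini–Hochberg adjustment lowers power below these values.

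The sample size and design do not change. The cost is a few sentences and a less favourable stated power.

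### The 95% power is quoted for one factor at a time, but significance requires a Benjamini–Hochberg-adjusted p below 0.05, so 95% does not hold for the rule that will be applied

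*Protocol article*

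**What the plan says.** All statements are in the Statistical analysis section of the protocol article. The analysis is one factor at a time: "Univariate Poisson regressions will be used to analyze the association of structural factors and relative-reported factors or structural data with the primary endpoint".

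Three power claims follow for 240 patients:
- The first covers a 50% change in rate, "corresponding to rate ratios of 1.5 and greater, given a base rate of 0.85". The claim is made "with a power of 95% if the influence variable is a binary categorical variable with 50% probability of occurrence".
- The second: "For a binary factor with a probability of occurrence of 90%, the detectable rate ratio with 95% power is still 2.0".
- The third: "For continuous, normally distributed influence variables, rate ratios of > 1.25 are detectable with 95% power".

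No alpha and no sidedness are given with these claims.

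The next paragraph sets the decision rule. It begins: "Since a large number of factors are to be tested, the adjustment for multiple testing seems reasonable". Significance is then reserved for P "values of the univariate regression analyses that are < 0.05 after adjustment with the" Benjamini–Hochberg procedure. A looser cut-off, adjusted p below 0.1, admits a factor to the multivariable model. The power claims do not mention the adjustment, the number of factors or the number of associations expected to be real.

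**The concern.** Power is the probability of meeting the rule by which a result will be called significant. Here the power claims and the rule stand in adjacent paragraphs and describe different tests. Under BH with m factors, the k-th smallest p-value is compared with 0.05 × k/m, which is well below 0.05 unless most factors are rejected.

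Two things are at stake. A reader told of 95% power would take a non-significant caregiver or structural factor as good evidence against a rate ratio of 1.5, which the design may not support. And because entry to the multivariable model also uses adjusted p-values, real predictors of the planned size can be left out of that model.

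**Working it through.** **Inputs from the protocol article:** N = 240; base rate 0.85, read here as the rate when the factor is absent; the three scenarios above; BH at 0.05 for significance and at 0.1 for model entry.

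**Assumptions:** ideal Poisson counts, all 240 patients contributing, two-sided p-values under BH, and the continuous rate ratio read as per standard deviation. The number of factors m is not stated, so 10 to 50 is used. Study measures and Study visits and data assessment list about 29 candidates: 4 WHOQOL-BREF domains, 3 further caregiver scores, 4 COVID-19 items, 2 surprise questions, 6 caregiver characteristics, 2 for amount and type of professional support, 1 for living situation and 7 patient items from the records (4 + 3 + 4 + 2 + 6 + 2 + 1 + 7 = 29).

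**Step 1: reproduce the 95%.** For a binary factor with prevalence π, Var(log RR) = [1/(1−π) + 1/(π·RR)] / (N × 0.85), with N × 0.85 = 204.
- RR 1.5, π = 0.5: Var = (2 + 1.333)/204 = 0.01634, SE = 0.1278, log 1.5 = 0.4055, ratio = 3.172. Two-sided 5%: Φ(3.172 − 1.960) = 0.887. One-sided 5%: Φ(3.172 − 1.645) = 0.937. Direct Poisson simulation gives 0.893 and 0.940.
- RR 1.25, continuous: Var = 1/(204 × exp(0.2231²/2)), ratio = 3.227. Two-sided 0.897, one-sided 0.943; simulation 0.887 and 0.935.
- RR 2.0, π = 0.9: the result depends on the approximation. The Wald formula gives ratio 3.047, so 0.862 two-sided and 0.920 one-sided. Poisson simulation gives 0.931 (Wald) to 0.946 (likelihood ratio) two-sided, and 0.970 to 0.975 one-sided.

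With the null variance taken at the mean rate for the binary factors, all three claims come within 2 points of 95% as single one-sided 5% tests (0.941, 0.966, 0.943). As two-sided tests, RR 1.5 and RR 1.25 do not reach 95%.

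**Step 2: a bound that needs no m.** The BH cut-off 0.05 × k/m never exceeds 0.05, because k ≤ m. Two-sided power under BH therefore cannot exceed the single-test value, which is about 89% for RR 1.5.

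**Step 3: the size of the loss.** BH was simulated with independent normal test statistics (100,000 replicates). The true effects had mean 3.172 (RR 1.5, 50% prevalence). Average power per true factor:

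| m | 1 true | 3 true | 5 true | half true |
|---|---|---|---|---|
| 10 | 0.648 | 0.751 | 0.808 | 0.808 |
| 20 | 0.567 | 0.662 | 0.722 | 0.805 |
| 30 | 0.517 | 0.607 | 0.670 | 0.805 |
| 50 | 0.464 | 0.538 | 0.598 | 0.805 |

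A correlation of 0.3 between the statistics changes such values by about 1 point. As a hand check, the first BH step at m = 30 has cut-off 0.05/30 = 0.00167, z = 3.144, and Φ(3.172 − 3.144) = 0.511, close to 0.517.

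**Step 4: grant the plan a genuine two-sided 95%.** The mean is then 1.960 + 1.645 = 3.605. At m = 30, BH leaves 0.686, 0.773 and 0.822 with 1, 3 and 5 true effects, and 0.909 if half are true. Over m = 10 to 50 the range is 0.63 to 0.91.

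**Step 5: entry to the multivariable model.** With BH at 0.1, RR 1.5 and m = 30, the probability of entry is 0.610, 0.707 and 0.766 with 1, 3 and 5 true effects, and 0.881 if half are true.

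**The case against.** The study calls itself explorative, and BH controls the false discovery rate whatever the power, so what is declared significant is no less valid. The looser 0.1 screen recovers part of the loss for the multivariable model. Power per single test is a common planning convention, and the list of candidates may well stand in a full protocol or analysis plan that is not shown. All of this is fair. It limits the consequence to an optimistic planning statement and more missed predictors, and the unstated number of factors is not itself a fault of the article. It does not make 95% right for a rule printed in the next paragraph.

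Three stronger readings are tempting, and the document does not support them:
- A reader might infer that real power is 50–70%. That range needs roughly 20–30 factors with 1–5 true effects, and the document fixes neither number. If half the factors matter, power is about 80%.
- A reader might charge the whole shortfall to BH. For RR 1.5, about 6 points (95% to 88.7%) arise before any adjustment if p-values are two-sided. BH then takes a further 22 to 37 points at m = 30 with 1–5 true effects (88.7 − 67.0 and 88.7 − 51.7), but only about 8 if half are true (88.7 − 80.5).
- A reader might conclude that a one-sided test was planned. The figures fit one best, but alpha and sidedness are not stated, so this stays an inference.

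**Conclusion.** The point holds as a mismatch between the basis of the power claims and the significance rule. The 95% figures are close to right only for a single unadjusted test, and all three together only if it is one-sided. For the rule to be applied, power at RR 1.5 is at most about 89% with two-sided p-values. Given 10 to 50 factors and anything from one true effect to half of them true, it is about 46–81%. Even a genuine two-sided 95% falls to about 69–82% at 30 factors with 1–5 true effects, and no scenario run at the 0.05 rule reaches 95%.

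These sizes rest on assumed numbers of factors and true effects, ideal Poisson variation and complete data on 240 patients. Overdispersion, or fewer than 240 caregiver datasets, would lower them further; neither is counted here. The figures for RR 2.0 depend on the approximation and are not used to size the problem.

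**What to change.** In the Statistical analysis section:
1. Label the present figures as power for a single unadjusted test, and state the alpha and sidedness behind them.
2. If two-sided p-values will be used, replace them with two-sided values, for example about 89% instead of 95% for RR 1.5 at 50% prevalence.
3. Add power under BH at 0.05, and the probability of entry at 0.1, for the actual number of candidate factors and a few assumed numbers of true effects, laid out like the table above.

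This takes a few sentences and a short simulation. Recruitment, data collection and the analysis itself stay as they are. The only downside is a less favourable stated power. Restricting BH to a short list of factors is not needed to correct the error and is not proposed.
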